#### Demographic and other baseline characteristics

Participants’ demographics (age and gender), socioeconomic attributes (marital status, education level, and average monthly income), lifestyle (smoking habits and alcohol consumption), and comorbidity will be collected through a structured questionnaire to prevent the influence of confounding factors such as demographics and other baseline variables on the results.

#### Data management

Participant’s information will be retained, except for their names, personal identities, or any other information that might reveal their identity. The results of the study and samples will be attached to a list using a special code. Only authorized researchers will be allowed to view the list. Data transferred to a dedicated server via the smartphone app will be encrypted. The dedicated server is installed in the Fujian Geriatrics Center.

### Statistical analysis

All data will be processed and analyzed using IBM SPSS 22.0 statistical analysis software, and a significance level of 5% will be used. Independent *t*-tests or *Mann–Whitney* tests will be used to compare demographic and other baseline characteristics of participants pre-intervention. A two-way ANOVA test with repeated measures for each of the variables will be applied to assess the effect of the program at pre-intervention, post-intervention, and follow-up stages on complexity (non-linear measures) vs. traditional (linear) measures of the proportion of pre-frailty, BC vs. BMD, PA vs. sedentary behaviors, FF (4-m gait speed test, TUG test, chair sit and reach test, back scratch test, single leg stance test, HGS, and 30-s chair rise test), and inflammatory cytokines. A subgroup analysis of the intervention group will be conducted after 12-month follow-up to explore the potential impact of continued exercise on the sustainability of the intervention effects. Multiple equation chain interpolation (MICE) is used to handle missing data, and where missing data are associated with observed covariates, propensity scores may be used to weight observations or adjust models to balance groups defined by missing data status. Statistical analyses will be performed using per-protocol and intent-to-treat (ITT) analyses in the case of potential dropouts.

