## Methods

### Study design and setting

This is an open-label, prospective, two-arm parallel RCT with balanced randomization (1:1), allocation concealment, and outcome assessment blinding. The study protocol employs the Standard Protocol Items: Recommendations for Interventional Trials (SPIRIT) guideline and the Consolidated Standards of Reporting Trials (CONSORT) statement for clinical trial transparency (29). The trial will be conducted at the Fujian Geriatrics Center, which is the largest geriatrics specialty among general hospitals in Fujian Province, China. Participants will be recruited from the *Fujian Prospective Aging Cohort* according to the screening criteria and randomly allocated to two groups: the *PF-Life* program (intervention) group and the health education (control) group. Data from each participant group will be collected at four different times: screening assessment, post-randomization baseline assessment, 4-month outcome assessment, and 12-month outcome assessment. The flowchart of the study protocol is displayed in Figure 1.

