### Sample size

The sample size is calculated using the statistical software PASS v11.0 (NCSS, Kaysville, UT, United States). Based on previous studies (32, 33), the proportion of reversing a pre-frailty state in the health education group and exercise groups is assumed to be 10 and 40%, respectively. Using a two-sided Fisher’s exact test and considering a dropout of approximately 20% (34, 35), the trial requires 118 participants (59 in each group, 50% each) to obtain 90% certainty (power = 1-*β*) of detecting a statistical difference at *α* = 0.05 (two-sided) level of significance. In order to increase the efficacy of the study, a total of 140 individuals will be recruited in this study (70 in each group).

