### Randomization, blinding, and allocation concealment

To ensure allocation concealment, participants will be randomly assigned to the *PF-Life* group or control group in a 1:1 ratio by study staff (who will not be involved in participant recruitment or outcome assessment). The random number sequence will be generated by the investigator using a simple randomization procedure.^1^ These random numbers will then be individually placed in sequentially coded, sealed, opaque envelopes. The researcher will open the envelopes sequentially and assign random numbers to participants to identify their group. In addition, participants and interventionists will be instructed not to disclose the allocation to outcome assessors and data analysts. Unblinding will occur after all data analyses have been completed and will be carried out by staff not directly involved in the study.

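### Baseline variables are collected to prevent confounding, but for the arm comparison the plan states only baseline significance tests and an effect analysis that names no covariate; pre-specified adjustment would serve the purpose at almost no cost

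*Protocol article*

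**What the plan says.** Four places in the protocol article bear on this.

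- **Demographic and other baseline characteristics.** Age, gender, marital status, education, monthly income, smoking, alcohol use and comorbidity are recorded. The reason given is "to prevent the influence of confounding factors such as demographics and other baseline variables on the results".
- **Randomization, blinding, and allocation concealment.** The sequence is produced "using a simple randomization procedure". No stratification or blocking is mentioned.
- **Statistical analysis, baseline.** Independent t or Mann–Whitney "tests will be used to compare demographic and other baseline characteristics of participants pre-intervention".
- **Statistical analysis, program effect.** A two-way ANOVA with repeated measures "will be applied to assess the effect of the program at pre-intervention, post-intervention, and follow-up stages". The proportion with pre-frailty is among the variables listed, and no covariate is named. Covariates are mentioned once more, for missing data: where missingness is associated with observed covariates, "propensity scores may be used to weight observations or adjust models to balance groups defined by missing data status".

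**The concern.** Recording a variable prevents nothing. It can protect a comparison only through the design (stratified allocation) or the analysis (adjustment). The article states simple randomization, and its effect analysis names no covariate. The one step it states for these variables in comparing the arms is a baseline significance test. That test cannot do the job: under proper randomization any baseline difference is due to chance, so its p-value tests a hypothesis already known to be true. A non-significant result does not show that an imbalance is harmless, and a significant one changes no estimate.

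The named tests also do not fit all the variables. A t or Mann–Whitney test is not suited to a nominal item such as marital status.

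At stake are protection against a chance imbalance in a prognostic factor and some precision in the primary comparison. Both could be had from data already being collected.

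**Working it through.** **1. Reproduce the plan's own figure.** Inputs from Sample size: 10% v 40% reversal, two-sided Fisher's exact test, α = 0.05, 90% power, about 20% dropout. By exact enumeration, power is 89.8% at 46 per arm and 90.6% at 47. Then 47 / 0.8 = 58.75, rounded up to 59 per arm, or 118 in total. This matches. With 70 recruited per arm, 70 × 0.8 = 56 remain, and Fisher power is 95.3%.

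**2. Chance of a significant baseline test.** For the eight listed variables, taken as independent: 1 − 0.95^8 = 0.337, or 34%.

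**3. Size of imbalance such a test can miss.** The standard error of a standardized baseline difference is √(2/n), so the 5% threshold is 1.96 × √(2/n). That is 0.33 SD at 70 per arm and 0.37 SD at 56 per arm.

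**4. What that imbalance and adjustment do.** The documents give no covariate–outcome association, so its strength is an assumption shown as a range. The simulation used 4,000 trials per row, 56 per arm, 10% v 40%, and one standardized covariate. It compared the unadjusted analysis with logistic adjustment standardized to a risk difference; power is by likelihood-ratio test.

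| Log-odds per SD (assumed) | Variance ratio, adjusted / unadjusted | Power, unadjusted → adjusted | Shift in unadjusted risk difference at about 0.37 SD imbalance | Shift after adjustment |
|---|---|---|---|---|
| 0 | 1.00 | 97.0 → 97.0% | 0.0 points | 0.0 |
| 0.5 | 0.98 | 97.1 → 97.3% | +3.0 points | +0.2 |
| 1.0 | 0.88 | 97.2 → 98.6% | +4.9 points | +0.1 |
| 1.5 | 0.79 | 97.4 → 99.2% | +6.3 points | −0.1 |

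At an assumed smaller effect, 10% v 30%, power goes from 78.2 to 79.8%, from 78.7 to 83.8%, and from 78.2 to 87.8% for log-odds 0.5, 1.0 and 1.5.

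**5. Two covariates together.** A second simulation (3,000 runs, 56 per arm, linear probability model) adjusted for age (assumed log-odds 0.5–0.8 per SD) and for entry with one or two frailty components (assumed control reversal 16% v 4%). Variance fell by 7.8–11.3% over three scenarios. Power went from 96.2 to 97.2% in one. In the other two, with about half the planned effect, it went from 69.9 to 71.4% and from 66.0 to 69.7%.

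**6. Where that gain comes from.** Run separately under the same assumptions, age alone cut variance by about 2.5% (log-odds 0.5) to 5.5–6.6% (0.8). Component count alone cut it by 5–7%. Component count is not among the variables listed in the demographics section, although Table 1 records the frailty phenotype at screening and baseline.

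**7. Continuous secondary outcomes.** The variance factor is 1 − ρ²: 0.99, 0.91, 0.75 and 0.51 for an assumed ρ of 0.1, 0.3, 0.5 and 0.7.

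**8. Events available.** 56 × 0.10 + 56 × 0.40 = 5.6 + 22.4 = 28 reversals.

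**The case against.** The strongest reply is that this rests on silence. A condensed article may leave its covariate list to a fuller document, and naming no covariate is not the same as declaring the analysis unadjusted. That stands for the list itself. It does not cover the baseline tests, which are a stated choice and cannot serve the stated purpose.

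Three stronger readings are tempting, and the documents support none of them.

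- **That baseline testing is the only planned use of these variables.** Observed covariates may also enter the propensity adjustment and possibly the multiple imputation, and Table 1 lists medical and demographic data among its exploratory items. The propensity step is optional and balances groups by missing-data status, so it does not deal with imbalance between arms.
- **That the primary comparison is confounded or invalid.** Under randomization the unadjusted difference is unbiased on average, and its interval already allows for chance imbalance. The shifts in step 4 are conditional on an unlucky allocation.
- **That valuable precision is being thrown away.** All prognostic strengths are assumed. Much of the 8–11% reduction comes from frailty component count rather than from demographics and comorbidity, and at the planned effect power is already about 95% or more.

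The 34% figure also assumes independence. Age, education, income and comorbidity are probably correlated, and the article attaches no action to these p-values.

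**Conclusion.** The point holds in a limited form. The purpose stated for collecting the baseline variables is not served by the stated analysis, and two of the eight items, gender and marital status, are nominal variables that the named tests do not suit. The consequence is exposure to chance imbalance and some lost precision, not bias on average.

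On the assumed strengths, adjustment reduces the variance of the risk difference by about 0–2% for weak covariates, 8–12% for moderate ones and about 20% for very strong ones. At 10% v 40% that is worth about one power point (range zero to two). At 10% v 30% it is worth about 2, 5 and 10 points for log-odds 0.5, 1.0 and 1.5. The planned sample size does not need to change. The change is worth making because it is nearly free, not because the primary conclusion depends on it.

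**What to change.** 1. Replace the baseline tests with a table by arm: n (%), mean (SD) or median (IQR), without p-values.
2. Pre-specify a short covariate list for the 12-month primary outcome, for example age, sex and baseline frailty component count, with comorbidity if events allow. Use a model suited to a binary outcome, such as logistic regression with a standardized risk difference. Apply it whatever balance is observed. Age and sex could be carried into the secondary models.
3. If adjustment is not wanted, reword the sentence on preventing confounding so that it claims no protection the analysis does not give.

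**Cost.** Analysis wording only; the variables are already collected. The estimate becomes slightly more complex because it needs standardization. With about 28 expected events, three covariates plus arm leave 28 / 4 = 7 events per coefficient, and a fourth covariate leaves 28 / 5 = 5.6, so the list must stay short. The test also needs care at this size. In a null simulation (20% in both arms, log-odds 1.0), the adjusted likelihood-ratio test rejected in 6.0% of trials against 5.3% unadjusted, so the method for the p-value and interval should be checked and fixed in advance.

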### Participants and recruitment

We aim to include 140 participants in this 1-year RCT. Recruitment will be carried out through posters, lectures, and flyers at the community health centers where the project team previously conducted the *Fujian Prospective Aging Cohort* Study. The cohort study was conducted in five community centers in Fuzhou, China, with a prevalence of pre-frailty of 44% (30). Participants inclusion criteria are: (1) aged ≥60 years; (2) living in the community; (3) fulfilling one or two of the Fried frailty phenotypes (31); (4) a smartphone user; (5) being able to walk independently without an assistive device; and (6) having normal language expression and comprehension (speaking Mandarin). Exclusion criteria are: (1) acute myocardial infarction within the past 3 months; (2) unstable or persistent cardiovascular or respiratory condition; (3) moderate to severe cognitive impairment, psychiatric disorders that prevent cooperation; (4) traumatic fracture (within 6 months); (5) performing moderate-to-vigorous PA more than 150 min per week during the past 3 months; and (6) inability to exercise or other conditions that may interfere with exercise.

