### Primary outcome assessment

The primary outcome is the proportion of participants with pre-frailty in the intervention group compared with the control group over 12 months from baseline, as measured by the Fried frailty phenotype, which is currently an internationally recognized standard for frailty identification and assessment. The frailty criteria have five components (29): (i) unintentional weight loss (>4.5 kg or at least 5% of body mass in the previous year through a self-reported questionnaire); (ii) low handgrip strength (HGS, cutoff points: ≤30 kg for males and ≤18 kg for females); (iii) fatigue [self-reported using questions 7 and 20 of the Centre for Epidemiological Studies Depression Scale (CES-D)]. Study participants are asked how often in the past week they think they have had difficulty completing daily tasks and how often they have been unable to complete activities. A positive response of ‘most of the time’ or ‘always’ to either question is considered an indication of fatigue; (iv) slow gait (≥0.65 m/s walking speed over a 4.5 m distance); and (v) low PA levels (<383 kcal/week for males and <270 kcal/week for females). The presence of one or two of the five components is recognized as pre-frailty.

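### The yes/no primary outcome is assigned to a three-visit repeated-measures ANOVA that names neither the arms nor a time point, although the trial is sized on Fisher's exact test of two proportions

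*Protocol article*

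**What the plan says.** - **Outcome (Primary outcome assessment).** The article defines its main endpoint as follows: "The primary outcome is the proportion of participants with pre-frailty in the intervention group compared with the control group over 12 months from baseline". The state is binary: "The presence of one or two of the five components is recognized as pre-frailty".
- **Entry (Participants and recruitment).** Eligibility requires "fulfilling one or two of the Fried frailty phenotypes", so everyone is pre-frail at screening.
- **Sizing (Sample size).** The proportion reversing "in the health education group and exercise groups is assumed to be 10 and 40%, respectively". The test is named too: "Using a two-sided Fisher’s exact test and considering a dropout of approximately 20" per cent. No time point is attached to the two rates.
- **Analysis (Statistical analysis).** The method is "A two-way ANOVA test with repeated measures for each of the variables will be applied to assess the effect of the program". Three stages are covered: before the intervention, after it, and at follow-up. The list of measures begins thus: "complexity (non-linear measures) vs. traditional (linear) measures of the proportion of pre-frailty, BC vs. BMD, PA vs. sedentary behaviors". Functional fitness and cytokines come next. No method for binary data is named. The only two-group tests mentioned are for baseline characteristics.
- **Populations (same section).** "Statistical analyses will be performed using per-protocol and intent-to-treat (ITT) analyses in the case of potential dropouts". The two are not ranked here, although the Discussion says that analyses follow ITT principles.

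**The concern.** The article states three things about the primary outcome that do not fit together. The outcome is a between-arm comparison of a proportion. The sample size is for an exact test of two proportions. The analysis is a two-way ANOVA over three stages whose listed pairs set one outcome against another. The complexity and non-linear measures in the first pair are defined nowhere in the article.

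This is more than detail left to an analysis plan, because a method is positively assigned to the primary outcome and it conflicts with the method used for sizing. At stake is what a significant primary result would mean. By the Exercise program section, the advised training period is 16 weeks and use of the program afterwards is optional. An effect that appears at 16 weeks and then fades is therefore a realistic possibility, and the plan should be able to tell it from an effect that lasts.

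**Working it through.** **1. The plan's own sample size.** Inputs from the Sample size section: 10% v 40%, two-sided α = 0.05, power 90%, dropout 20%. Full binomial enumeration of the two-sided Fisher test gives power 0.898 at 46 per arm and 0.906 at 47, so 47 evaluable per arm are needed. Then 47 / (1 − 0.20) = 58.75, rounded up to 59 per arm, or 118 in total. The stated figure reproduces exactly, which confirms that the trial was planned around a direct comparison of two proportions.

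**2. What each test asks.** Let d0, d16 and d12 be the differences between arms in the proportion reversed at baseline, 16 weeks and 12 months. Eligibility makes d0 zero or close to it.
- Fisher at 12 months tests d12 = 0.
- The arm-by-visit interaction tests d0 = d16 = d12. With d0 = 0 this means d16 = 0 and d12 = 0 together, so a difference at either visit is enough to reject.
- The arm main effect tests (d0 + d16 + d12) / 3 = 0. With differences of 0, 30 and 0 points the average is 10 points, so it too can reject with no 12-month difference.

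**3. How much this matters.** The favourable reading (arm by visit) was simulated with 140 × 0.80 = 112 evaluable, or 56 per arm, and baseline constant. The interaction statistic is F = (SS_arm×visit / 2) / (SS_error / 220), where 220 = 2 × 2 × (56 − 1). The visit-specific rates and the latent within-person correlation are assumptions. The 10% and 40% are the planning rates, and 23% is the pre-frail-to-healthy transition rate given in the Background. There were 2,000 to 5,000 runs per scenario.

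| Reversal at 16 weeks, control v PF-Life | Reversal at 12 months | Latent correlation | Arm × visit rejects | Fisher at 12 months rejects |
|---|---|---|---|---|
| 10% v 40% | 23% v 23% | 0.5 | 96% | 3% |
| 10% v 40% | 10% v 10% | 0.5 | 98% | 2% |
| 10% v 40% | 10% v 10% | 0.3 / 0.7 | 97% / 99% | 2% / 2% |
| 10% v 40% | 10% v 20% | 0.3 / 0.7 | 93% / 95% | 21% / 24% |
| 10% v 20% | 10% v 10% | 0.5 | about 30% | as for other 10% v 10% rows |
| 10% v 10% | 10% v 10% | 0.3 / 0.7 | 5% / 4% | 2% / 2% |
| 10% v 40% | 10% v 40% | 0.3 / 0.7 | 99% / 98% | 95% / 95% |

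In the third row the arm main effect rejects in 84% and 77%. A Greenhouse–Geisser correction leaves the interaction at 96% and 99%.

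**4. Power of the direct comparison.** Exact Fisher power for 10% v 40% is 0.953 with 56 per arm, 0.961 with 59 and 0.984 with 70.

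**The case against.** The strongest defence is that the wording is loose but the intent is clear. A two-way analysis of the program's effect, in a two-arm trial whose primary outcome compares the arms, most likely means arm by time. That is fair, and the garbled pairs do not show that outcomes will really be tested against each other. But the simulation already grants this reading, and the problem remains.

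A second defence is that the primary outcome is described as over 12 months, not at 12 months. If the target spans follow-up, a real difference at 16 weeks is part of it and rejecting is not a false success. This stands in part: the 12-month time point is the natural reading, not the literal text. If it is not intended, the time point is unfixed, and an omnibus test still cannot say when the arms differ.

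Third, a full 30-point effect that vanishes is extreme. That is why the 30% figure for a milder effect is shown beside it.

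Several stronger readings are tempting and are not supported:
- **Inflated type I error or lost power.** Baseline status has little or no variance, which breaks the ANOVA assumptions, but rejection under a full null is 4–5% and power for a sustained effect is 98–99%.
- **No effect size obtainable.** Differences between cell means of a 0/1 variable are risk differences. What is lacking is a stated estimate with a suitable interval.
- **Missing visits dropped, ITT absent.** Multiple imputation is planned and the Discussion commits to ITT. Only the ranking of the two populations is missing from the analysis section.
- **Repeated-measures ANOVA wrong for continuous outcomes.** It is a legitimate choice. Baseline adjustment there is an optional gain in efficiency.

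**Conclusion.** The stated primary analysis is wrong as written and should be corrected before the data are analysed. A binary outcome is assigned to ANOVA, the assignment contradicts the Fisher-based sizing, and neither a between-arm contrast nor a time point is fixed. The fault is the hypothesis tested. In the assumed worst case (10% v 40% at 16 weeks, no difference at 12 months) the omnibus test rejects in about 96–98% of trials, against 2–3% for the direct 12-month comparison. With an assumed 10% v 20% transient effect it rejects in about 30%. These figures rest on assumed visit-specific rates, a latent correlation of 0.5 (0.3 and 0.7 give similar results for the worst case), 56 evaluable per arm, the arm-by-visit reading, and 12 months as the intended time point. If the effect is sustained, both approaches would usually reach the same answer.

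**What to change.** Rewrite the analysis paragraph to state the following:
- **Primary analysis.** Between-arm comparison of the proportion reversed at 12 months, in the ITT population with the planned multiple imputation, by the Fisher's exact test used for sizing or by logistic regression. Report the risk difference with a 95% CI. Logistic regression and the risk difference are easier to pool over imputations. Covariates should be few, since 10% of 56 is only about 6 expected control events.
- **Definition of reversal.** Zero Fried components. Under the present definition a participant who progresses to three or more components also ceases to be pre-frail. The rule should make clear that such a participant counts as not reversed.
- **Ranking.** 16 weeks is secondary and per-protocol is a sensitivity analysis.
- **Model terms.** Replace the three outcome-against-outcome pairs with arm, visit and arm-by-visit terms for the repeated-measures analyses.

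The cost is one rewritten paragraph. No extra data are needed, and with 95% Fisher power at 56 evaluable per arm the recruitment target of 140 does not change.

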### Secondary outcomes

Secondary outcomes are the change in BC, FF, bone mineral density (BMD), inflammatory cytokines, PA, and sedentary behaviors.

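### The repeated-measures ANOVA for the continuous secondary outcomes treats the baseline value as an outcome level, adjusts for no baseline value and does not say which term tests the program

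*Protocol article*

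**What the plan says.** The Secondary outcomes section defines the targets as changes: "Secondary outcomes are the change in BC, FF, bone mineral density (BMD), inflammatory cytokines, PA, and sedentary behaviors". The Statistical analysis section gives one method for all of them: "A two-way ANOVA test with repeated measures for each of the variables will be applied to assess the effect of the program". The same sentence names the stages, the test being "applied to assess the effect of the program at pre-intervention, post-intervention, and follow-up stages". They match the baseline, 4-month and 12-month visits listed under Study design and setting ("screening assessment, post-randomization baseline assessment, 4-month outcome assessment, and 12-month outcome assessment").

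The section does not name the two factors. It does not say whether group, time or their interaction is the test of the program, and it names no baseline-value covariate. The only model adjustment it mentions is an optional propensity-score one for missing-data status. The tests are at 5% ("a significance level of 5% will be used").

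Table 1 schedules every one of these outcomes at baseline, 16 weeks and 1 year.

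**The concern.** The program cannot have acted before it starts, yet the analysis speaks of "the effect of the program at pre-intervention, post-intervention, and follow-up stages" and counts the pre-intervention visit as one of them. Three terms come out of such an ANOVA, and they answer different questions:

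- **Group main effect:** compares the arms on the mean of all three visits. One third of that mean comes from a visit with no effect.
- **Time main effect:** asks whether both arms together changed. Retest learning, ageing or season can produce this with no program effect.
- **Group-by-time interaction:** does test differential change, but as a 2-df omnibus test on unadjusted change. By itself it gives no between-arm difference at 16 weeks or 12 months.

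At stake are the readings on body composition, bone density, functional tests, activity and cytokines. If the group main effect is used, real effects are likely to be missed. If the time effect is read as the program's effect, a shared drift is reported as benefit. If the interaction is used, some precision may be given up although the baseline values are already collected.

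**Working it through.** **The plan's own figure.** The Sample size section concerns only the binary primary outcome: 10% v 40% reversal, two-sided Fisher's exact test, "0.05 (two-sided) level of significance", 90% power and about 20% dropout. Exact enumeration gives power 0.898 at 46 per arm and 0.906 at 47. Then 47/0.8 = 58.75, rounded up to 59 per arm, or 118. This agrees with "the trial requires 118 participants (59 in each group, 50% each) to obtain 90% certainty". Nothing here disturbs that figure.

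**Inputs.** Recruitment is 70 per arm, so n = 70 × 0.8 = 56 per arm after dropout. The two-sided 5% level is from the article. Assumed, because the article gives none: SD 1, equal correlation ρ between the three visits, and true effect d. Arms are equal at baseline by randomization. Power is from the noncentral F distribution.

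**Sustained effect (0, d, d at the three visits).** Noncentrality λ:

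- Group main effect: the difference is 2d/3 and the variance of a person's three-visit mean is (1+2ρ)/3, so λ = 2nd²/[3(1+2ρ)], with 1 and 110 df.
- Interaction: the squared deviations of (0, d, d) from their mean sum to 2d²/3, so λ = nd²/[3(1−ρ)], with 2 and 220 df.
- Adjusted mean of both later visits: residual variance (1−ρ)(1+2ρ)/2, so λ = nd²/[(1−ρ)(1+2ρ)], with 1 and 109 df.
- Adjusted comparison at one visit: residual variance 1−ρ², so λ = nd²/[2(1−ρ²)], with 1 and 109 df.

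Example at d = 0.4, ρ = 0.5, where nd² = 56 × 0.16 = 8.96. In the same order, λ = 17.92/6 = 2.99; 8.96/1.5 = 5.97; 8.96/1 = 8.96; 8.96/1.5 = 5.97. The interaction and the single-visit comparison have equal λ here. They differ in power because one spends 2 df and the other 1.

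Power at d = 0.4, in percent:

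| ρ | Group main effect | Interaction | Adjusted, one visit | Adjusted, mean of two visits |
|---|---|---|---|---|
| 0.3 | 48 | 43 | 60 | 80 |
| 0.5 | 40 | 58 | 68 | 84 |
| 0.7 | 35 | 81 | 84 | 94 |
| 0.8 | 32 | 94 | 94 | 98 |
| 0.9 | 30.5 | 99.9 | 99.8 | 100 |

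From unrounded values, the interaction loses about 16, 10, 3, 0 and 0 points against the single-visit comparison, and about 37, 27, 13, 4 and 0 against the two-visit mean. The λ ratio of the two-visit mean to the interaction is 3/(1+2ρ): 1.88, 1.50, 1.25, 1.15 and 1.07.

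**Effect at 4 months only (0, d, 0).** The squared deviations again sum to 2d²/3, so the interaction keeps its power. The two-visit mean now carries d/2, so its λ falls to a quarter. At d = 0.4, ρ = 0.6 this is 10.18/4 = 2.55, giving 35% against 68% for the interaction. The adjusted 4-month comparison has 75%.

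**Time main effect with no program effect.** Assume both arms shift by 0.3 SD at both later visits. Then λ = 112 × (2/3) × 0.09/(1−ρ) = 6.72/(1−ρ), or 11.2, 16.8 and 33.6 at ρ = 0.4, 0.6 and 0.8. The time effect is significant in about 85%, 96% and 100% of trials. In simulation under this null, the between-arm tests, interaction included, stayed near 5%.

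**The case against.** The strongest reply is that group by time is the usual test of treatment in a parallel trial with this model. It matches secondary outcomes defined as change, and it holds its type I error. Nowhere does the article say that the group or time main effect will be read as the program's effect, and a condensed article may leave the choice of term to a fuller plan. All of that stands. A reader might infer that the trial will report time effects as benefit, or that its secondary analyses are biased. The text supports neither.

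The reply also holds that low power cannot be charged to the ANOVA as a whole. That stands too. At correlations of 0.8 or more the interaction gives up almost nothing, and the article does not tell us the correlation. The losses of up to 37 points use the comparator that a sustained effect favours. The Exercise program section prescribes 16 weeks of training and leaves later use to the participant, so a waning effect is plausible, and the averaged contrast can then do worse than the interaction. The single-visit figures also take each visit at 5%, so a correction for two visits would use up some of the gain.

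What the reply does not remove is the stated structure. Baseline as an outcome level is fixed in the text, and a value already serving as an outcome level cannot simply be added as a covariate by a later document. At low to moderate correlation, the visit-specific adjusted comparison is more powerful for either effect pattern, and it yields the estimate a reader needs.

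**Conclusion.** The point holds in a limited form. The group main effect should not be used as the program test: its dilution to 2d/3 for a sustained effect is algebra, and its power at d = 0.4 is about 30-48% over the assumed correlations. The time effect is not evidence about the program. The interaction is valid and unbiased. Its cost depends on the correlation: about 16 points against a visit-specific adjusted comparison at 0.3, about 3 at 0.7, and none from 0.8. A general claim that the planned ANOVA has power well below a baseline-adjusted analysis is therefore not supported.

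All power figures rest on 56 per arm, equal correlations between visits, normal outcomes and assumed d and ρ. The matter concerns precision and interpretation of secondary outcomes, and leaves the sample size unchanged. It is worth changing, but does not threaten the trial's validity.

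**What to change.** In the Statistical analysis section, for each continuous secondary outcome, replace the three-stage ANOVA with a linear mixed model on the 16-week and 12-month values. Use arm, visit and arm-by-visit as factors and the outcome's own baseline value as covariate. Report the adjusted between-arm difference with a 95% CI at each visit. An average over visits may be added, with the caution that it is weak if the effect fades. State that time effects and a three-visit group main effect are not evidence of a program effect.

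SPSS can fit this model, and no new measurements are needed. There is one small cost. Study design and setting places the baseline assessment after randomization in an open-label trial, so the covariate should be a value measured before the participant knows the allocation. The screening value would serve where Table 1 collects it: body composition, bone density, chair rise, arm curl, grip, and chair sit and reach. For the remaining tests, activity and cytokines, Table 1 shows no screening value, so the protocol should state that baseline is measured before allocation is disclosed, or arrange for it. The planned ANOVA has the same weakness, since it uses the same baseline.
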